#### Analysis of Maintenance Phase data

For the Maintenance Phase, we hypothesize that i) maintenance yoga will be non-inferior to maintenance PT; ii) maintenance yoga will be superior to no yoga maintenance; iii) maintenance PT will be superior to no maintenance PT; and iv) maintenance yoga and maintenance PT will both be superior to education. To test our hypotheses, we will perform longitudinal analyses on the pain and function outcomes incorporating all measurements across the study period, including baseline and 6, 12, 26, 40, and 52 weeks. We will perform a longitudinal profile analysis to compare the pattern of change in outcomes over the study period with a five-part treatment variable (yoga maintenance, yoga no maintenance, PT maintenance, PT no maintenance, education), time, and their interaction as predictors in the model. The initial model will assume an unstructured covariance to account for the correlation between repeated measures on an individual. A simpler model may be used for the covariance or the model for the means over time if found to be appropriate. No missing data will be replaced in these longitudinal analyses. All available patient data can be included and the analysis will be considered to be unbiased under a “missing at random” mechanism. Additional subgroup longitudinal analyses can be done using only data from those participants who were 12-week completers. We will also compare the change in pain medication usage over time using a generalized estimating equation approach or non-linear mixed effects model to account for the repeated measures of a dichotomous outcome. This approach will parallel the longitudinal analyses for continuous outcomes described above.

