**Figure 1 F1:**
[figure not shown]
**Study flow diagram.** The study will recruit 320 participants with chronic low back pain from Boston Medical Center and surrounding affiliated federally qualified community health centers. Participants are randomized after baseline data collection to yoga classes, physical therapy (PT), or education through a self-care book in a 2:2:1 ratio. This year-long study is divided into a 12-week Treatment Phase and subsequent 40-week Maintenance Phase. Yoga and PT participants who have attended at least one intervention session during the Treatment Phase are re-randomized at 12 weeks into a structured maintenance intervention or no structured maintenance intervention. For the participants, we term the no structured maintenance intervention as “Home Practice” only. Education participants continue through the study without any re-randomization.

For the subsequent 40-week Maintenance Phase, there are five separate groups. At the end of the Treatment Phase, yoga participants are re-randomized in a 1:1 ratio to either a structured ongoing maintenance yoga program or no structured maintenance. Similarly, PT participants are re-randomized in a 1:1 ratio to either a structured ongoing maintenance PT program or no structured maintenance. Yoga and PT participants randomized to no structured maintenance are encouraged to continue with home practice. Education participants are not re-randomized and are encouraged to continue to review and follow the recommendations of their educational materials. For the Maintenance Phase, we hypothesize: i) maintenance yoga will be non-inferior to maintenance PT; ii) maintenance yoga will be superior to no yoga maintenance; iii) maintenance PT will be superior to no maintenance PT; and iv) maintenance yoga and maintenance PT will both be superior to education.

In addition, we collect data on medical utilization, out-of-pocket direct and indirect medical costs, implementation costs, and health-related quality of life to compare the cost-effectiveness of yoga, PT, and education from three perspectives: society, third-party payer, and the participant. We hypothesize that yoga will be more cost-effective than PT. Individual interviews using a semi-structured interview guide will be analyzed using qualitative methods. This study was approved by the Boston University Medical Campus (BUMC) Institutional Review Board.

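### The profile comparison named as the test of the Maintenance Phase hypotheses has no margin, so it cannot decide the non-inferiority hypothesis, and it is weaker than a targeted contrast for the superiority hypotheses

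*Protocol article*

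**What the plan says.** The section on analysis of Maintenance Phase data opens with four hypotheses. The first, also given under Study Design, is that "maintenance yoga will be non-inferior to maintenance PT". The second and third are that maintenance beats no maintenance within yoga and within PT. The fourth is that "maintenance yoga and maintenance PT will both be superior to education".

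The method follows directly: "To test our hypotheses, we will perform longitudinal analyses on the pain and function outcomes incorporating all measurements across the study period". The visits are listed as "including baseline and 6, 12, 26, 40, and 52 weeks". The analysis is then named: "We will perform a longitudinal profile analysis to compare the pattern of change in outcomes over the study period with a five-part treatment variable", with "time, and their interaction as predictors in the model". On the covariance: "The initial model will assume an unstructured covariance to account for the correlation between repeated measures on an individual".

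For this phase the article gives no pairwise contrast, time point, margin, alpha or sidedness. The margins of 1.0 point (pain) and 1.5 points (RMDQ) under Sample size considerations are introduced for change from baseline to week 12. The same section expects adequate power for the Maintenance Phase but gives no figure.

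**The concern.** A profile analysis asks whether the groups' mean curves over time have the same shape. That does not match what is hypothesised, for three reasons.

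- **Hypothesis i is a non-inferiority statement.** The null of a profile comparison is equality. A non-significant result does not bound how much worse maintenance yoga might be, and a significant one gives neither the direction nor the visit.
- **The five-group test covers weeks 0 to 52.** Yoga, PT and education differ by randomization from baseline, so a benefit over education gained by week 12 is itself a difference in profile. The joint test can reject on that alone, with no maintenance effect.
- **Hypotheses ii to iv are pairwise and directional.** Spreading the test over 5 or 20 degrees of freedom costs power compared with one contrast aimed at the visits where maintenance can act.

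One of the trial's three specific aims rests on this analysis. The 12-week co-primary comparisons do not.

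**Working it through.** **The plan's own figures.** With SD 2.5, margin 1.0, one-sided alpha 0.05 and 90% power, n = 2 × [2.5 × (1.645 + 1.282) / 1.0]² = 107.1, so 108 per arm as stated. For function, 1.5 / (4.35 × √(2/107)) = 2.522, and 2.522 − 1.645 = 0.877, giving power 0.81 as stated. There is no Maintenance Phase figure to reproduce.

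**Inputs from the article.** SD of change 2.5 (pain) and 4.35 (RMDQ); 128 yoga, 128 PT, 64 education; 1:1 re-randomization, so 64 in each of five groups; 20% dropout, so 0.8 × 64 ≈ 51.

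**Assumptions (not in the article).** The SD of change applies between any two visits; equal correlation rho between visits; true effects of 1.0 (pain) and 1.5 (function), constant at weeks 26, 40 and 52; two-sided 0.05 for superiority; large-sample tests. The within-person variance is then SD²/2: 3.125 for pain and 9.461 for function.

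**1. Two-group profile test, maintenance versus none (5 df).** Noncentrality = (n/2) × SS / (SD²/2), where SS is the sum of squared deviations of the six visit differences from their mean. For pain, differences (0, 0, 0, 1, 1, 1) give SS = 1.5. For function, SS = 1.5 × 1.5² = 3.375.
- Pain, n = 51: 25.5 × 1.5 / 3.125 = 12.24, power **0.78**.
- Function, n = 51: 25.5 × 3.375 / 9.461 = 9.10, power **0.63**.

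**2. Targeted 1-df contrast: mean of weeks 26, 40 and 52, adjusted for weeks 0, 6 and 12.** Conditional variance = σ² × [(1 + 2rho)/3 − 3rho²/(1 + 2rho)], with σ² = SD² / (2(1 − rho)). At rho = 0.5 the bracket is 0.6667 − 0.375 = 0.2917.
- Pain: 6.25 × 0.2917 = 1.823; SE = √(2 × 1.823/51) = 0.267; z = 3.74; power **0.96**.
- Function: 18.92 × 0.2917 = 5.519; SE = √(2 × 5.519/51) = 0.465; z = 3.22; power **0.90**.
- Over rho 0.4 to 0.6 the ranges are 0.96–0.97 and 0.89–0.91.

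**3. Joint five-group test (20 df) when maintenance yoga is truly worse by the 12-week pain margin.** With one group differing from the other four, noncentrality = n × (4/5) × SS / 3.125. With 64 per group this is 24.58 and power is 0.88; with 51 it is 19.58 and power is 0.76. The test is therefore non-significant with probability 0.12 to 0.24 although yoga is worse by the full margin.

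**4. Joint test with a Treatment Phase benefit only.** Let all four active groups beat education by 0.7 at week 6 and 1.4 at week 12, with no difference between maintenance and no maintenance. If the 1.4 persists, the mean difference over six visits is 1.05 and SS = 1.05² + 5 × 0.35² = 1.715. If it vanishes after week 12, the mean is 0.35 and SS is again 1.715. Noncentrality is 64 × 0.8 × 1.715 / 3.125 = 28.1 (rejection probability **0.93**), or 22.4 with 51 per group (**0.83**).

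**5. Do the early visits cause the power loss?** Dropping weeks 0 and 6 and testing from week 12 (3 df) gives SS = 0.75 and, with n = 51, noncentrality 6.12 and power 0.53, against 0.78 with all visits. The early visits help.

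**6. Can the model answer hypothesis i?** Take the yoga-minus-PT mean over weeks 26 to 52, adjusted for baseline only, rho = 0.5, no true difference, 12-week margins carried over. Pain: variance 6.25 × (0.6667 − 0.25) = 2.604; SE = √(2 × 2.604/51) = 0.320; 1.0/0.320 − 1.645 = 1.48; power 0.93. Function: SE 0.556; 1.5/0.556 − 1.645 = 1.05; power 0.85.

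**The case against.** The strongest reply is that treatment, time and their interaction with an unstructured covariance is a full means model. Any difference between two groups, at any visit or averaged, can be drawn from it with a confidence limit. The article nowhere says that a joint interaction P value decides the hypotheses or that non-significance will be read as non-inferiority. Naming contrasts is often left to an analysis plan, which is not shown, and the margins rest on minimal important differences that could carry forward.

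Much of this stands. A reader might infer that the planned model cannot address non-inferiority; step 6 shows that it can. The reply fails on one point: the article does not leave the test open. It says how the hypotheses will be tested and names a comparison of patterns of change. For the Treatment Phase it gives test, sidedness, time point and margin. A stated method that does not fit its hypothesis is more than omitted detail.

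A reader might also infer that including visits before re-randomization dilutes the tests or produces false positives. The article does not support that. Step 5 shows the early visits add precision. For maintenance versus none, chance early differences are already covered by the nominal error rate: in the step 4 scenario the yoga maintenance versus no-maintenance test rejects with probability 0.05. For hypotheses i and iv, differences at weeks 6 and 12 are not chance at all, because those arms were randomized at baseline.

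**Conclusion.** The concern holds for the test, not for the model or the data. Followed as written, the profile comparison cannot decide hypothesis i, because no margin enters it. The five-group version can be significant with no maintenance effect (probability 0.83 to 0.93 in the scenario shown). For maintenance versus none, the profile test gives up about 18 percentage points of power for pain and 27 for function.

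The sizes rest on assumed retention, effect size, effect shape and correlation. For a sustained effect the direction is the same across rho 0.3 to 0.7. The advantage needs a contrast that suits the shape of the effect. With 51 per arm, rho 0.5 and a pain effect of 1.0 at week 52 only, a week-52 contrast has power 0.72, the 5-df profile test 0.49 and the mean of weeks 26 to 52 only 0.24.

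This should be corrected because a specific aim depends on it. The 12-week co-primary conclusions are untouched.

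**What to change.** Keep the mixed model and all six visits. Replace the profile comparison as the decision test with one pre-specified contrast per hypothesis on visits after week 12: either the mean of weeks 26, 40 and 52, or week 52.

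- **Maintenance versus none (ii, iii):** use weeks 0, 6 and 12 for adjustment, with the two yoga sub-arms sharing a common mean before re-randomization, and likewise the two PT sub-arms.
- **Across the arms randomized at baseline (i, iv):** adjust for the baseline score only, since weeks 6 and 12 already carry treatment effects.
- **Hypothesis i:** compare a one-sided 95% confidence limit with a stated margin, for example 1.0 and 1.5 points if the sponsor confirms that the 12-week margins carry over.
- **Interaction test:** report it descriptively.

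The cost is analysis wording only, with the same data and model family. The downside is committing in advance to one time summary, which is less sensitive if the effect takes another shape.

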### Randomization for 40-week Maintenance Phase

At the completion of the 12-week Treatment Phase, all participants who were initially randomized to the yoga arm and have attended at least one yoga class are re-randomized in a 1:1 ratio to either a structured ongoing maintenance yoga program for 40 weeks or no structured maintenance. Similarly, all participants who were initially randomized to the PT arm and have attended at least one PT session during the 12-week Treatment Phase are re-randomized in a 1:1 ratio to either a structured ongoing maintenance PT program for 40 weeks or no structured maintenance. Yoga and PT participants that did not go to any sessions during the 12-week Treatment Phase do not continue into the Maintenance Phase. Education participants continue into the Maintenance Phase without any re-randomization. They are encouraged to continue to review and follow the recommendations of their educational materials. Re-randomization of yoga and PT participants into their new treatment arms for the Maintenance Phase is done by the study biostatistician ([name]) who has no contact with participants, knowledge of any participant identifying information, or other involvement in enrollment or randomization processes. Each participant eligible for the maintenance phase was assigned a random number using the random uniform function in SAS. For yoga and PT separately, the lower half of random numbers were assigned to maintenance and the larger half of numbers to no maintenance. Participants are notified of their re-randomization group after their 12-week survey by unblinded study staff. A password protected spreadsheet on the study’s network drive is used to document when and how participants are notified of their re-randomization assignment.

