#### Sample size considerations

For the co-primary endpoints of change in pain or function from baseline to week 12, we assume a one-sided α error = 0.05. If we assume a minimal clinically significant difference of 2.0 points for the 11-point pain intensity scale, then using a 1.0 point non-inferiority margin for pain is reasonable [103]. If we assume 3.0 points on the 23-point RMDQ scale is a minimal clinical significant difference, then choosing a non-inferiority margin of 1.5 for function is reasonable [105]. A common standard deviation of change in all groups is 2.5 points for the 11-point pain intensity scale and 4.35 points for the 23-point RMDQ function scale [24,26].

Using these assumptions, 108 participants in both the yoga and PT group would provide 90% power to detect whether yoga is truly non-inferior to PT in respect to effect on pain. Similarly, 107 participants in both the yoga and PT group would provide 81% power to detect whether yoga is truly non-inferior to PT in respect to effect on function. Using these sample sizes, we would be able to detect at least a 1.4 unit difference in pain or at least a 2.4 difference in function with 90% power for superiority of yoga or PT compared to education. We inflated these sample sizes in order to protect against an estimated dropout rate of 20%. With this adjustment, the target sample size for the yoga and PT groups is 128 participants each. Using a yoga:PT:education 2:2:1 randomization scheme, we need a total of 320 participants (128 yoga, 128 PT, 64 education). Thus, for the co-primary outcomes of pain and function at 12 weeks, we have adequate power to determine non-inferiority between yoga and PT and superiority of yoga and PT to education*.*

We also anticipate adequate power for the longitudinal analyses of the Maintenance Phase data. Incorporation of repeated measures over time increases power by increasing the “effective sample size,” which is a function of the number of participants and the number of total measurements (0, 6, 12, 26, 40, and 52 weeks). Participants who drop-out or who have missing data can still be included in these analyses.

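### The Maintenance Phase model for the means over time may be simplified on the trial data, and a smooth trend that ignores the week-12 re-randomisation is not excluded

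*Protocol article*

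**What the plan says.** Under Analysis of Maintenance Phase data, pain and function are analysed longitudinally, "incorporating all measurements across the study period, including baseline and 6, 12, 26, 40, and 52 weeks". The starting model for the means is a profile analysis "with a five-part treatment variable (yoga maintenance, yoga no maintenance, PT maintenance, PT no maintenance, education), time, and their interaction as predictors in the model". On the covariance: "The initial model will assume an unstructured covariance to account for the correlation between repeated measures on an individual". The section then adds: "A simpler model may be used for the covariance or the model for the means over time if found to be appropriate". It gives no criterion for appropriateness and no limit on which mean models may replace the starting one.

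Under Randomization for 40-week Maintenance Phase, yoga participants with at least one class attended "are re-randomized in a 1:1 ratio to either a structured ongoing maintenance yoga program for 40 weeks or no structured maintenance"; PT participants are handled the same way. The timing is explicit: "Participants are notified of their re-randomization group after their 12-week survey by unblinded study staff".

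**The concern.** Maintenance and no-maintenance sub-arms come from one randomised arm and learn their allocation only after the 12-week survey. At weeks 0, 6 and 12 they can therefore differ only by chance, and a maintenance effect can appear only at weeks 26, 40 and 52. Three of the six visits in the model carry no such effect. A smooth group-by-time trend over all six visits lets those three visits pull on the later contrasts.

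The hypotheses that maintenance yoga and maintenance PT each beat no maintenance rest directly on these contrasts. The comparisons of maintenance yoga with maintenance PT, and of both with education, come from the same model. If the simpler trend is chosen because it seems to fit, its standard errors are reported as though it had been fixed in advance. The question is whether a fit check would catch a wrong trend, and how large the error would be if it did not.

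**Working it through.** **Inputs from the protocol article.** Visits at 0, 6, 12, 26, 40 and 52 weeks. From Sample size considerations: "A common standard deviation of change in all groups is 2.5 points for the 11-point pain intensity scale and 4.35 points" for function; 128 in each of yoga and PT; 20% dropout. Sub-arm size: 128 × 0.8 / 2 ≈ 51.

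**Assumed, not in the document.** Compound symmetry with within-person correlation ρ = 0.3, 0.5 or 0.7; the shape of the true effect; a straight-line interaction as the simpler model, with the overall mean over time left categorical.

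**Reproducing the plan's own figure.** For non-inferiority on pain with margin 1.0, one-sided 5% and 90% power: n = 2 × 2.5² × (1.645 + 1.282)² / 1.0² ≈ 107.05, rounded up to 108 per arm, as stated. Power for function with 107 per arm and margin 1.5 is 81%, as stated. The article gives no power figure for the Maintenance Phase model.

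**Bias of the straight line.** Let d(t) be the maintenance minus no-maintenance difference. Mean visit time = 136/6 = 22.67; Sxx = 5160 − 6 × 22.67² = 2077.3. For a 1-point benefit from week 26, d = (0, 0, 0, 1, 1, 1), with mean 0.5 and Sxy = 118 − 6 × 22.67 × 0.5 = 50. The slope is 50/2077.3 = 0.02407 per week, so the fitted value is 0.5 + 0.02407 (t − 22.67):

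- week 12: 0.24 (truth 0)
- week 26: 0.58 (truth 1)
- week 40: 0.92 (truth 1)
- week 52: 1.21 (truth 1)

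**Standard errors.** σ² = 2.5² / [2(1 − ρ)]. With categorical visits, SE = σ√(2/51). With the line, SE² = (2/51)σ²[ρ + (1 − ρ)(1/6 + (t − 22.67)²/Sxx)]. Coverage = Φ(1.96 − |bias|/SE) − Φ(−1.96 − |bias|/SE).

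| ρ | SE, categorical (any visit) | SE, line (weeks 26 / 40 / 52) | Coverage, line (weeks 26 / 40 / 52) |
|---|---|---|---|
| 0.3 | 0.42 | 0.27 / 0.30 / 0.35 | 66 / 94 / 91% |
| 0.5 | 0.50 | 0.38 / 0.40 / 0.44 | 80 / 95 / 92% |
| 0.7 | 0.64 | 0.55 / 0.57 / 0.60 | 88 / 95 / 94% |

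Categorical visits give zero bias and 95% coverage throughout.

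**Would a fit check stop it?** The residual sum of squares of d about the line is 3 − 1.5 − 50²/2077.3 = 0.2965. The error variance for this test is (1 − ρ)σ² × 2/51 = 3.125 × 2/51 = 0.1225 whatever ρ is. The noncentrality is therefore 0.2965/0.1225 = 2.42 on 4 df, and the line passes a 5% test in 80% of trials. By AIC it is kept in about 71%. Coverage at week 26 after the lack-of-fit choice is 71–89%.

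**Other shapes, by the same formula.**

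- Effect 1, 0.5, 0 at weeks 26, 40, 52: bias −0.73 at week 26 and +0.42 at week 52.
- Effect 0, 0.5, 1: bias +0.31 at week 26 and −0.21 at week 52.
- Linear growth from 0 at week 12 to 1 at week 52: bias at most 0.06 at weeks 26 to 52, coverage 94–95%.
- No effect: no bias, and coverage about 94–95% even after data-driven choice.

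A line with a knot at week 12 does not remove the problem: under the 1-point step it still gives −0.42 at week 26 and +0.20 at week 52, because it forces linear growth after week 12.

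**The case against.** The starting model is sound, the sentence is only permissive, and a condensed article may leave the selection rule to an analysis plan that is not shown. That holds as far as it goes: the document does not say that a straight line will be used. But the permission is stated text, it covers the means as well as the covariance, and it is open-ended as written.

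A reader might infer that the Maintenance Phase intervals will not cover 95%. The documents do not support that. The error needs both the simplification to be used and an effect that is not roughly linear over the 52 weeks. With no true effect there is no bias and coverage stays near nominal, so the superiority tests do not gain a material excess of false positives this way.

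Nor is the error uniform. Week 26 is the worst visit, week 40 is nearly unaffected under the step, and the errors largely cancel in an average over the three visits: (−0.42 − 0.08 + 0.21)/3 ≈ −0.10. It might also be inferred that the non-inferiority conclusion is seriously exposed. In the one scenario simulated, with a late loss of yoga equal to the 1.0 margin, false non-inferiority was 8–10% against 5–7% for the full group-by-visit model: a modest excess.

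Finally, not every simplification of the means is wrong. Setting the paired sub-arms equal through week 12 follows from the design, and a blanket ban would forbid it.

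**Conclusion.** The point holds in conditional form. The plan permits a data-judged simplification of the means and does not exclude a trend that ignores week 12. Under an early step effect, a fit check would usually let that trend through. For a 1-point step in pain, the week-26 effect is then shrunk by about 0.4 points with coverage of 66–88%, and the week-52 effect is overstated by about 0.2 with coverage of 91–94%. Under no effect, or linear growth after week 12, bias is at most about 0.06 and coverage about 93–95%.

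These figures rest on compound symmetry, 51 complete participants per sub-arm, the protocol's SD of change of 2.5, and assumed effect shapes. The 12-week co-primary t-tests do not use this model and are unaffected. The change is worth making because the shape of the effect cannot be known in advance.

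**What to change.** Replace the permissive sentence. For all Maintenance Phase hypothesis tests, keep visit categorical with group-by-visit means and an unstructured covariance. Allow one simplification of the means, fixed in advance: the two yoga sub-arms, and the two PT sub-arms, share their means through week 12. Allow a named simpler covariance, with robust standard errors, only if the model does not converge. Report smoothed trends as descriptive.

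The cost is one sentence and no new data. The starting model has 5 × 6 = 30 means and 6 × 7 / 2 = 21 covariance parameters, which about 320 participants can support. Intervals are wider than under a fitted trend: at ρ = 0.5 the week-26 SE is 0.50 against 0.38. The equality constraint multiplies the categorical SE by √[1 − 3ρ²/(1 + 2ρ)]. At ρ = 0.5 this is √0.625, giving 0.39 and recovering most of the loss. At ρ = 0.7 it gives 0.40, below the line's 0.55. At ρ = 0.3 it gives only 0.38, against 0.42 without the constraint and 0.27 for the line, so there the loss of precision largely remains.
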